### Sample size

2.12

The sample size for the current study was based on a statistical superiority trial (continuous data) design of a randomized control trial. To verify that a new treatment is more effective than a standard treatment from a statistical point of view or from a clinical point of view, its corresponding null hypothesis is that the new treatment is not more efficacious than the control treatment by a statistically/clinically relevant amount. Based on the nature of the relevant amount, a superiority design contains statistical superiority trials and clinical superiority trials.^[26]^

Where N is the size per group, *p* the response rate of standard treatment group; *p* 0 the response rate of new drug treatment group; *z* the standard normal deviate for a 1 or 2 sided *x*; *d* the real difference between 2 treatment effect; a clinically acceptable margin; and S is the Polled standard deviation of both comparison groups. 

Calculating the sample size using the equation above: 

N = 35

The sample size calculated from statistical superiority for randomized control trial is 35 for each arm of the treatment, so altogether 70 euvolemic hypertensive patients should be recruited for the current study. Since a 25% dropout rate has to be anticipated, the final total was 88:44 in each arm.

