### Standard and intervention arms

2.7

Both the standard and intervention arms will be randomized with equal numbers of patients. The standard-arm patients will receive antihypertensive therapy except RAAS inhibitors that included calcium-channel blockers, diuretics, alpha- and beta-blockers, whereas the intervention-arm patients will be prescribed ARB (losartan) alone or in combination with standard antihypertensive pharmacotherapy. In both study arms, patients will be allowed multiple antihypertensive pharmacotherapies to control BP, after discussion with a panel of experts. However, this will only be done where entirely necessary to avoid any deterioration to a patient's health. Finally, study intervention (losartan) and antihypertensive medication will be given to the patients on a weekly basis by the principle investigator. A member of patient's family will be consented to monitor a patient's adherence at home whereas a pill check will be performed once a week. Only the study participants will be blinded during the course of study.

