### Statistical analysis

2.13

Results will be expressed as mean or percentage. Comparisons between treatment groups will be made by using a Wilcoxon test after adjustment for the dynamic stratification variables (age, sex, years on dialysis, and diabetes). Cohen d test will be applied to note the effect size. In addition, linear and logistic regression will be applied to note any influence of patient characteristics on treatment outcome. This data will be presented as hazard ratios and 95% confidence intervals. Statistical significance will be set at *P* less than 0.05. All statistical calculations will be performed using Statistical Package for the Social Sciences (SPSS) version 20. Figure 1 provides details of study flow diagram.

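### The 25% dropout allowance multiplies by 1.25 instead of dividing by 0.75, so 44 per arm leaves 33 patients, below the 35 required

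*Protocol article*

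**What the plan says.** Section 2.12 (Sample size) of the protocol article gives three figures in sequence.

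- The requirement per arm: "The sample size calculated from statistical superiority for randomized control trial is 35 for each arm of the treatment".
- The corresponding total: "so altogether 70 euvolemic hypertensive patients should be recruited for the current study".
- The recruitment target after allowing for dropout: "Since a 25% dropout rate has to be anticipated, the final total was 88:44 in each arm".

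Section 2.7 (Standard and intervention arms) fixes equal allocation: "Both the standard and intervention arms will be randomized with equal numbers of patients". The article does not define the 25% in any other way, for instance as a margin added on top of the completers.

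**The concern.** A dropout rate is a proportion of the patients enrolled. To end with a required number of completers, that number is divided by one minus the rate. Adding 25% to the required number is a different operation and gives too small a target. The figures of 44 and 88 look like the result of adding 25%.

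If so, the trial could recruit exactly to target, lose exactly the proportion it expected to lose, and still finish with fewer patients than its own calculation calls for. Whatever power the 35 per arm was meant to provide would not be reached under the plan's own assumption. The article shows no other reserve, and its limitations section (3.1) already names the small sample as a main weakness.

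**Working it through.** **Inputs** (section 2.12, with 1:1 allocation from section 2.7)

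- Required per arm: n = 35 (total 70)
- Anticipated dropout: d = 0.25
- Stated target: 44 per arm (total 88)

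**Step 1. Reproduce the stated target.**

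n × (1 + d):

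- per arm: 35 × 1.25 = 43.75, rounded up to 44
- total: 70 × 1.25 = 87.5, rounded up to 88

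Both stated figures are reproduced exactly.

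**Step 2. Apply the stated dropout to the stated target.**

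- per arm: 44 × (1 − 0.25) = 33, against 35 required
- total: 88 × (1 − 0.25) = 66, against 70 required

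**Step 3. Find the target that does keep 35.**

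n / (1 − d) = 35 / 0.75 = 46.67, rounded up to 47 per arm, 94 in total.

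- Check: 47 × 0.75 = 35.25, which meets the requirement; 46 × 0.75 = 34.5, which does not.
- Difference from the stated target: 3 per arm, 6 in total. Rounding does not explain it.

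**Step 4. Find the dropout that 44 per arm can absorb.**

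1 − 35/44 = 9/44 = 20.5%.

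**Step 5. Size of the power loss (conditional).**

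The base figure of 35 could not be rebuilt. The equation and its inputs (difference, standard deviation, margin, power) are not legible in the text available. Section 2.12 leaves the test's direction open ("the standard normal deviate for a 1 or 2 sided *x"), and section 2.13 sets the level ("Statistical significance will be set at *P* less than 0.05"). The power figures below therefore rest on assumptions: a two-sample comparison of means, normal approximation, 5% level, and a design power of either 80% or 90% at 35 per arm.

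The standardised difference implied by 35 per arm is δ = (z_α + z_power) / √(35/2). Power at 33 per arm is Φ(δ × √(33/2) − z_α).

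| Assumed test | Assumed power at 35 | Implied δ | Power at 33 |
|---|---|---|---|
| two-sided 5% | 80% | 0.670 | 77.65% |
| two-sided 5% | 90% | 0.775 | 88.25% |
| one-sided 5% | 80% | 0.594 | 77.92% |
| one-sided 5% | 90% | 0.700 | 88.43% |

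The loss is about 2 percentage points in every row, so the open question of one or two sides hardly matters here. Steps 1 to 4 do not depend on any of these assumptions.

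**The case against.** Four points can be made for leaving the figure as it is.

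1. **The effect is small.** Two patients per arm and about 2 points of power lie well within the usual uncertainty of an assumed standard deviation or dropout rate, and no estimate or test is biased. This stands. It limits the weight of the point but does not make the figures agree.

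2. **Some patients who leave early may still contribute.** Blood pressure is recorded at every dialysis session (section 2.10), and the primary end point in section 2.8 is control held for 4 weeks, which a patient could reach before leaving. So 33 is strictly a count of expected completers. This stands only in part. The abstract describes a comparison from baseline to 12 months, and the purpose of a dropout allowance is to replace patients treated as lost. If they counted in full, no allowance would be needed.

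3. **The power loss is not established.** No design power is legible, the analysis named in section 2.13 is a Wilcoxon test, and the end point in section 2.8 is a responder definition. This stands for the exact percentages, which are illustrative. The shortfall in numbers does not depend on them.

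4. **Adding a percentage is a common shortcut.** The section calls the 25% a dropout rate. Under that meaning the shortcut does not deliver 35 per arm, however widely it is used.

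**Conclusion.** The target is wrong as written. Under the plan's own 25% dropout, 44 per arm (88) leaves 33 per arm (66), short of the 35 (70) required by 2 per arm. The target that matches the stated requirement and rate is 47 per arm (94); the stated one holds only for dropout up to 20.5%.

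This rests on figures printed in one section and on reading the 25% as a proportion of randomised patients whose outcome is lost, which is how the section presents it. The consequence is modest: roughly 2 points of power if the design was set at 80% or 90%. It should be corrected, but it does not threaten the validity of the trial.

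**What to change.** Restate the dropout sentence in section 2.12, for example:

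> Randomising 44 patients per arm (88 in total) provides 35 evaluable patients per arm if dropout is at most about 20%. At the anticipated dropout of 25%, 33 per arm are evaluable, giving a power of [value] for the difference and standard deviation assumed above.

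The authors have to supply the power value, because it depends on the inputs to their own calculation.

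The cost is one sentence and the open statement of a power about 2 percentage points below the design value. No extra patients are needed. This is the practical route, since the abstract reports that enrolment has already begun.

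If 35 evaluable patients per arm at 25% dropout is a firm requirement, the target becomes 47 per arm (94 in total), which costs 6 additional patients.

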### Statistical analysis

2.13

Results will be expressed as mean or percentage. Comparisons between treatment groups will be made by using a Wilcoxon test after adjustment for the dynamic stratification variables (age, sex, years on dialysis, and diabetes). Cohen d test will be applied to note the effect size. In addition, linear and logistic regression will be applied to note any influence of patient characteristics on treatment outcome. This data will be presented as hazard ratios and 95% confidence intervals. Statistical significance will be set at *P* less than 0.05. All statistical calculations will be performed using Statistical Package for the Social Sciences (SPSS) version 20. Figure 1 provides details of study flow diagram.

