**Method and analysis::**

A single center, prospective, randomized, parallel design, single-blind trial will be conducted in the Malaysian state of Kelantan among postdialysis euvolemic hypertensive patients that are on regular dialysis at least 3 times a week. The primary outcome of the trial will be to note the effectiveness of losartan (RAAS inhibitor) in reducing systolic BP < 140 mm Hg compared to standard non-RAAS-inhibitor antihypertensive therapy. The secondary outcome will be to look at all causes of mortality. A body composition monitor (BCM) will be used to assess postdialysis volume and dry weight. Postdialysis euvolemic patients that have systolic BP > 140 mm Hg will be randomized using Covariate Adaptive Randomization to standard or treatment arm. Participants in the treatment arm will be given 50 mg of losartan once daily except on dialysis days, whereas the standard arm patients will be prescribed non-RAAS antihypertensive agents. The study participants will be followed for a period of 12 months. A Wilcoxon statistical test will be performed to note the difference in BP from baseline up to 12 months using Statistical Package for the Social Sciences (SPSS) 20.

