### Randomization of participants

2.5

Covariate adaptive randomization will be used to assign all prescreened participants that agree to participate in the study to the treatment or standard arm. Covariate adaptive randomization has an advantage over other randomization techniques in that it is able to achieve balance over a large number of covariates when the sample size is small to medium.^[22]^ The Taves covariate adaptive randomization method will be used for randomization to allow for the examination of previous participant group assignments in order to make a case-by-case decision on group assignment for each individual who enrol in the study. Using covariate adaptive randomization, patients will be assigned to the treatment or control arm. Based on expert opinion and preexisting literature, the covariates considered for this study will be: age, gender, diabetes, and year of dialysis. In order to avoid bias, randomization will be done by a computer programme, hence minimizing the risk of selection biasness and avoiding any influence of the researcher, the prescriber, or the participant on selection of group or medication. It is important to mention however that Scott et al^[23]^ argued that predictability and bias of randomization is true for all methods and so should not be overly penalized.

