### Study end point

2.8

A medication dose of 50 mg losartan per day for 3 weeks will be initiated as a test dose to note any incidence of hypotension. If there is no hypotensive event, patients will continue with 50 mg daily every day except dialysis days. The dose could be a titrated dose up to 100 mg/day, depending upon expert opinion and clinical scenario. As for treatment group, the dose titration would be initiated with losartan 50 to 100 mg followed by non-RAAS antihypertensive agents. As for standard group, the choice of dose titration would be left to expert opinion. The primary end point will be achieved by having a postdialysis BP of <140/90 mm Hg and maintaining this for 4 weeks. The secondary end point will be looking at all causes of mortality.

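### The between-arm test is given as a Wilcoxon test with an unnamed covariate adjustment, the abstract describes it differently, and recorded baseline BP is not used as a covariate

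*Protocol article*

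**What the plan says.** Section 2.13, Statistical analysis: "Comparisons between treatment groups will be made by using a Wilcoxon test after adjustment for the dynamic stratification variables". The variables listed are age, sex, years on dialysis and diabetes. They match the allocation factors in section 2.5, where "the covariates considered for this study will be: age, gender, diabetes, and year of dialysis" and "The Taves covariate adaptive randomization method will be used for randomization".

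The abstract gives another description: "A Wilcoxon statistical test will be performed to note the difference in BP from baseline up to 12 months". It mentions no adjustment and does not say whether the rank-sum or the signed-rank test is meant.

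Section 2.13 adds that "Results will be expressed as mean or percentage" and that "linear and logistic regression will be applied to note any influence of patient characteristics on treatment outcome". The regressions are introduced as additional and are aimed at patient characteristics. The treatment comparison itself rests on the Wilcoxon test. The level is fixed: "Statistical significance will be set at *P* less than 0.05".

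Section 2.8, Study end point, defines a responder outcome: "The primary end point will be achieved by having a postdialysis BP of <140/90 mm Hg and maintaining this for 4 weeks". The Sample size section describes a superiority design for continuous data.

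**The concern.** Neither the rank-sum nor the signed-rank test has a covariate term. As worded, the main comparison could be any of several procedures: an unadjusted rank test, a rank test stratified by the four factors, or a rank test on covariate-adjusted residuals. The abstract adds a further candidate, a test on change from baseline.

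These procedures perform differently after minimisation. Balancing the arms on prognostic factors and then ignoring those factors in the analysis overstates the standard error, so the test becomes conservative and loses power. Stratifying on all four factors spreads a small sample thinly. None of these candidates uses baseline BP as a covariate, and none by itself gives an adjusted difference in mm Hg with a confidence interval. In a trial whose own limitations name the small sample, power could be about 0.6 or above 0.9, depending on a choice that the text leaves open.

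**Working it through.** **1. The plan's own figure.** The article states 35 per arm (70 in total), raised to 44 per arm for 25% dropout. The second step reproduces as 35 × 1.25 = 43.75, rounded up to 44. The 35 cannot be reproduced, because the text at hand gives no effect, SD or power. Inverting the two-means formula for two-sided 0.05 and 80% power (both assumed) gives

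d = √(2/35) × (1.960 + 0.842) = 0.67 SD.

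This is used below as the alternative.

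**2. Simulation set-up.** Taken from the article: 70 analysed patients, 1:1 allocation, Taves minimisation on four factors, alpha 0.05. Assumed: two-sided testing, four binary factors of equal weight, a normal outcome with SD 1, factors explaining 0 to 30% of outcome variance, and a baseline–outcome correlation of 0 or 0.5. There were 4,000 runs per null setting (Monte Carlo SE √(0.05 × 0.95/4000) = 0.003) and 2,000 per alternative (SE about 0.009).

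**3. Type I error (baseline correlation 0).**

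| Variance explained | Unadjusted Wilcoxon | Van Elteren, 16 strata | Wilcoxon on residuals | ANCOVA, four factors |
|---|---|---|---|---|
| 0% | 0.057 | 0.054 | 0.063 | 0.058 |
| 10% | 0.041 | 0.058 | 0.060 | 0.051 |
| 20% | 0.032 | 0.052 | 0.056 | 0.052 |
| 30% | 0.020 | 0.049 | 0.060 | 0.055 |

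The unadjusted test becomes conservative as the factors become prognostic. The adjusted procedures stay close to nominal, with the residual version slightly above it.

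**4. Power at d = 0.67 (baseline correlation 0.5).**

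| Variance explained | Unadjusted Wilcoxon | Van Elteren, 16 strata | Wilcoxon on residuals | ANCOVA, four factors | ANCOVA, four factors + baseline |
|---|---|---|---|---|---|
| 0% | 0.766 | 0.606 | 0.782 | 0.790 | 0.883 |
| 10% | 0.775 | 0.648 | 0.828 | 0.836 | 0.934 |
| 20% | 0.776 | 0.694 | 0.858 | 0.860 | 0.954 |
| 30% | 0.802 | 0.747 | 0.910 | 0.912 | 0.984 |

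Over both baseline correlations the stratified test ranged from 0.61 to 0.77 and the unadjusted test from 0.77 to 0.80. The weakness of the stratified test follows from cell size: 2⁴ = 16 cells, 70/16 = 4.4 patients per cell, about 2 per arm.

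**5. Does the abstract's change from baseline already capture the gain?** With equal variances at both times and correlation ρ, relative to the follow-up variance, the change score has variance 2(1 − ρ) and ANCOVA has 1 − ρ². At ρ = 0.5 the change score gives 2 × 0.5 = 1, no better than ignoring baseline, while ANCOVA gives 0.75. The ratio of ANCOVA to change score is (1 − ρ²)/(2(1 − ρ)) = (1 + ρ)/2. For ρ from 0.3 to 0.6 this is 0.65 to 0.80, so ANCOVA has 20 to 35% less variance.

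**6. Effect of baseline on validity.** With baseline added at correlation 0.5, the ANCOVA type I error was 0.048 to 0.054. Omitting baseline costs power and does not distort the error rate.

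**The case against.** The strongest reply is that this is a condensed article, and that naming the exact adjusted rank procedure belongs in an analysis plan that is not shown. That stands as far as missing detail goes. It does not cover the rest: the article commits to a method, describes it in two ways that do not match, and confines the covariate models to patient characteristics.

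Several stronger readings are tempting and should be set aside.

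- A reader might infer that an adjusted Wilcoxon test cannot be carried out. Stratified and residual-based rank tests exist, and both ran at 70 patients with error close to 5%.
- A reader might infer an inflated error rate, or that the analysis will in fact be unadjusted. Section 2.13 says it will be adjusted. If it were not, the error would move in the conservative direction, and only if the factors are prognostic.
- A reader might take the abstract to mean a within-arm signed-rank test, and then blame regression to the mean after selection on high BP. Section 2.13 speaks of comparisons between treatment groups, and the abstract sets losartan against standard therapy. Any such figure would also assume that the qualifying readings serve as baseline, which the article does not say.
- A reader might say that baseline BP was left out of the adjustment list. That list is the dynamic stratification variables, and it agrees with section 2.5. Baseline BP was never one of them.
- Reporting means beside a rank test is a common descriptive choice and is no error in itself.

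**Conclusion.** The point holds as one of specification and efficiency. The named test does not match the stated adjustment, and the abstract and section 2.13 disagree. The range of permitted procedures runs from a power of about 0.61 to about 0.91 at 0.67 SD with 70 patients. An unadjusted test would have a true error of about 0.04 or 0.02 if the factors explain 10% or 30% of variance, and would be near nominal if they explain none. Using baseline BP as a covariate would lift ANCOVA power from about 0.79–0.91 to 0.88–0.98.

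These sizes rest on assumed prognostic strengths, a baseline correlation of 0.5, binary factors and a normal outcome; the documents give none of these. The documents do not support a claim that the planned comparison is impossible, biased or prone to false positives.

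**What to change.** For continuous postdialysis systolic BP, the scale of the abstract's test and of the sample size, replace the Wilcoxon sentence in section 2.13 with wording such as: arms are compared by ANCOVA with arm, baseline systolic BP, age, sex, diabetes and years on dialysis as covariates, and the adjusted mean difference in mm Hg is reported with its 95% confidence interval. State in advance which pre-treatment readings form the baseline. Keep a between-arm rank-sum test as sensitivity analysis.

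In the abstract, say that the test is between arms. Do not use within-arm change as evidence of effect.

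Reconcile this with section 2.8. If the responder end point is primary, analyse it with a logistic model on the same covariates, and report the ANCOVA as the continuous BP analysis.

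The cost is small. The four factors are needed for allocation, and Data handling and record keeping has BP noted at every dialysis session, so no new data are required. What is added is the usual linear-model assumptions, which the rank-sum sensitivity analysis covers. A logistic model with six terms in about 70 patients may also be unstable if responders or non-responders are few, so a fallback should be named in advance.

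### Section 2.13 promises hazard ratios from linear and logistic regression, and neither model gives one

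*Protocol article*

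**What the plan says.** The protocol article, section 2.13 (Statistical analysis), names three kinds of analysis.

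- **Comparison of arms:** "Comparisons between treatment groups will be made by using a Wilcoxon test after adjustment for the dynamic stratification variables". The abstract says what this test is applied to: "A Wilcoxon statistical test will be performed to note the difference in BP from baseline up to 12 months".
- **Effect size:** Cohen's d.
- **Supplementary regressions:** "linear and logistic regression will be applied to note any influence of patient characteristics on treatment outcome". The next sentence fixes how they are reported: "This data will be presented as hazard ratios and 95% confidence intervals".

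The outcomes are set in section 2.8 (Study end point). The primary one is attainment of a threshold: "The primary end point will be achieved by having a postdialysis BP of <140/90 mm Hg and maintaining this for 4 weeks". The secondary one is death: "The secondary end point will be looking at all causes of mortality". The abstract gives the length of follow-up: "The study participants will be followed for a period of 12 months".

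**The concern.** Each regression model has its own natural effect measure. A linear model gives a difference in means, here in mm Hg if the outcome is BP. A logistic model gives an odds ratio. A hazard ratio compares event rates over time and comes from a time-to-event model, which needs a time origin, an event time and a rule for censoring. Section 2.13 asks for the third measure from the first two models.

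The plan can then be carried out in one of two ways. Either the coefficients and odds ratios are printed under the wrong name, or a survival model that the article does not name is brought in to produce the promised measure. In the first case readers misjudge the size of the associations. In the second the model, time origin and censoring rule may be chosen after the data are seen.

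**Working it through.** The article gives no figure that depends on this sentence, so there is nothing to reproduce. The check has two parts.

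**1. Does any stated analysis yield a hazard ratio?**

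| Stated analysis | Applied to | Measure it yields |
|---|---|---|
| Wilcoxon test (abstract; section 2.13) | BP difference from baseline to 12 months | rank-based comparison |
| Cohen's d (section 2.13) | effect size | standardised mean difference |
| Linear regression (section 2.13) | treatment outcome | mean difference |
| Logistic regression (section 2.13) | treatment outcome | odds ratio |

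None does. The article mentions no Cox model, log-rank test, Kaplan-Meier estimate or censoring rule. Some Wilcoxon-type tests do belong to survival analysis, but the abstract ties this one to a BP difference, so that reading fails. The primary end point in section 2.8 is worded as reaching and holding a BP threshold, not as a time to an event. All-cause mortality is the end point for which a hazard ratio would be natural, and the article assigns it no analysis. The phrase therefore has nothing in the text to refer to.

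**2. How far apart are an odds ratio and a hazard ratio?**

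The article states no event probabilities, so those below are assumptions shown over a range. Take proportional hazards, complete follow-up to a fixed time, and event probability p0 in the reference group. Then:

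- p1 = 1 − (1 − p0)^HR
- OR = [p1/(1 − p1)] / [p0/(1 − p0)]

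Worked example with p0 = 0.50 and HR = 2.0: p1 = 1 − 0.50² = 0.75, so OR = (0.75/0.25)/(0.50/0.50) = 3.00.

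| Assumed p0 | OR when true HR = 1.5 | OR when true HR = 2.0 | OR/HR when HR = 2.0 |
|---|---|---|---|
| 5% | 1.52 | 2.05 | 1.03 |
| 20% | 1.59 | 2.25 | 1.13 |
| 50% | 1.83 | 3.00 | 1.50 |
| 70% | 2.18 | 4.33 | 2.17 |

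The last column is the odds ratio divided by 2.0. Mislabelling does little harm when events are rare. For a common outcome, which BP control under active treatment could well be, it overstates the effect substantially. For the linear model no conversion exists: a coefficient in mm Hg is not a ratio of any kind.

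**The case against.** The strongest reply is that this is a slip of wording in a supplementary analysis. The regressions are introduced as an addition and concern patient characteristics. They do not alter the Wilcoxon comparison, the end point definitions or the sample size of 88. An odds ratio under the wrong name is still a correctly estimated odds ratio, and for a rare outcome the two measures nearly coincide. All of this stands and limits the severity. It does not make the sentence correct, and no unseen analysis plan could make it correct as written.

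A reader might also infer more than the article supports:

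- **That the missing mortality model is a fault in itself.** A journal article may leave the model for a secondary end point to the full protocol or analysis plan. Its absence matters here only because it removes the one reading under which hazard ratios would fit.
- **That mortality will be analysed by logistic regression and so mishandle the 25% dropout.** The article does not say so. Section 2.12 uses the 25% only to enlarge the sample and does not say that vital status will be unknown for those patients.
- **That the trial is too small for a mortality comparison.** Whether or not that is so, it is a separate question and has no bearing on the label.
- **That every reported effect will be inflated.** The gap depends on the event probability, which the article does not give.

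**Conclusion.** Wrong as written, and of moderate severity. The mismatch between models and effect measure is plain from two consecutive sentences of section 2.13 and rests on no assumption.

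The size of the possible misreading does rest on assumptions: proportional hazards, complete follow-up and the chosen event probabilities. On those terms, for a true hazard ratio of 2.0, the odds ratio exceeds it by about 3% when 5% of the reference group have the event, and by 50% when half do. These figures illustrate the consequence of mislabelling; they do not predict this trial's results.

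**What to change.** The authors should first say which measure they meant, because two repairs are consistent with the text.

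1. **If the named models are right,** replace the reporting sentence with wording such as: *Linear regression results will be presented as adjusted mean differences and logistic regression results as odds ratios, each with a 95% confidence interval.*
2. **If hazard ratios were intended,** for all-cause mortality or for time to BP control, name the time-to-event model (for example Cox regression), the outcome it is applied to, the time origin and the censoring rule. Keep the term hazard ratio for that model only.

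The first repair costs one sentence and needs no new data. The second adds one standard model and needs event dates and last-contact dates. Neither changes the sample size or the Wilcoxon comparison. The choice should be fixed before the outcome data are analysed.
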